##### Parent education

Parent education is known to be an important component of early intervention that is grounded in family centred practice [33]. Since most of the infant’s active practice opportunities are provided in the child’ daily routines, parent education is vital [34]. In GAME intervention, parents are coached to identify their child’s voluntary attempts to move and self-regulate, plus understand the usual trajectory of emergent motor skills and how to stimulate progress. Parents are trained in simple motor task analysis and coached in appropriate strategies to enhance their child’s development both at a specific goal level and in general early learning and development principles. Parents are taught to optimise the best use of their infants’ “awake” time and the naturally occurring opportunities for learning. Learning optimisation includes both parent-directed and structured practice of desired motor tasks, where the parent role is integral to the child’s learning (e.g. creating repetitions) and constructing opportunities for independent play (e.g. playing alone with motor enriching toys set up for the child). Parents are encouraged to both observe the therapist eliciting a motor behaviour from the baby and to attempt it themselves. Specific feedback, in a warm and supportive context, is given to parents to enable them to tease out why some attempts were successful for the baby and others weren’t. As new motor skills emerge parents are coached in strategies to increase the challenge of the task; for example removal of support or the introduction of more complex toys. The importance of allowing trial and error during practice is discussed and parents are encouraged to devise their own activities to enhance goal attainment. Prognostic information is given when possible as well as evidence based information regarding sleeping, feeding and responsive parenting.

#### Game part 3

##### Environmental enrichment

It is clear that many aspects of a child’s environment influence his or her motor, cognitive and social-emotional outcomes. Parental responsivity, a variety of daily experiences, equipment use and the structure of the physical space are all known to influence child development [35-37]. In GAME, all visits are conducted within the family’s home and deliberate attention is paid to aspects of the home environment to enhance developmental outcomes. This enrichment includes assistance in setting up motor enriched play environments to promote child self-generated movements, exploration and task success. This includes instruction in careful toy selection “matched” to the desired motor task, plus physical set up of areas for practicing and repeating activities related to the identified goal areas, weightbearing, and reaching and grasping tasks. Conventional baby equipment (e.g. highchairs, toys) already purchased by the family is used wherever possible. The whole environment for motor learning is taken into account and therefore intervention may also include: (a) evidence-based early learning stimulation and role modelling to enhance cognitive and language development (e.g. reading books to children, limiting passive television watching); (b) optimising sleep hygiene; and (c) feeding interventions (e.g. anti-reflux medications) to ensure adequate caloric nutrition and pain-free backdrops for learning. The importance of variable daily experiences for infants is deliberately addressed and support given when parents articulate difficulty leaving the house. Siblings and extended family members are also actively encouraged to take part in the HP and therapy sessions to promote: family knowledge; family acceptance; family wellbeing; repetition of learning opportunities; and provide a natural source of varied social interaction for the infant. Parent well-being is openly discussed and support given to parents to access appropriate services when required.

Home visits from the GAME treating therapists are offered weekly initially and then frequency of intervention negotiated with each family around their preferences, availability and family resources required to carry out the intervention with fidelity. Visits are approximately 60 to 90 minutes duration.

### Standard care

“Standard care” (SC) describes the current follow-up and/or therapeutic interventions used when an infant deemed at high risk of CP is discharged from hospital in New South Wales Australia. It is not possible to standardise the frequency, intensity or type of interventions received in the SC group. Approaches used are varied and might include neurodevelopmental therapy, the developmental skills approach, group therapy or motor learning approaches reflective of the current EI literature base. Most therapists include parent education on positioning and handling and suggested home activities within the therapy programme. In the pilot study, SC therapy was offered approximately monthly but ranged from fortnightly to 3 monthly. In order to monitor the mode, frequency and intensity of intervention received by those in the standard care group as compared to the GAME group, all parents will be asked to keep a “log book” so that these relevant parameters can be compared between the groups. Similarly since the actual interventions provided in SC are likely to vary between services, history taking will include information gathering regarding the type of interventions used.

### Outcome measures and procedures

#### Peabody Developmental Motor Scales -Second edition (PDMS-2)

The PDMS-2 [38] is the primary outcome measure in this trial and is a frequently used assessment of motor skills. This test is standardised and normed for children aged from birth to 6 years and has been validated for use as a discriminative measure. Two studies have demonstrated that it is responsive to change in the CP population for both infants [39] and toddlers [40]. It has demonstrated concurrent validity with the GMFM [41] and the Bayley [42]. PDMS-2 assessments will be obtained at baseline, 16 weeks after therapy has commenced and at 12 months and 2 years. Assessments will be blind scored from video.

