**Methods/design:**

A two group, single blind randomised controlled trial (n = 30) will be conducted. Eligible infants are those diagnosed with CP or designated “at high risk of CP” on the basis of the General Movements Assessment and/or abnormal neuroimaging. A physiotherapist and occupational therapist will deliver home-based GAME intervention at least fortnightly until the infant’s first birthday. The intervention aims to optimize motor function and engage parents in developmental activities aimed at enriching the home learning environment. Primary endpoint measures will be taken 16 weeks after intervention commences with the secondary endpoint at 12 months and 24 months corrected age. The primary outcome measure will be the Peabody Developmental Motor Scale second edition. Secondary outcomes measures include the Gross Motor Function Measure, Bayley Scales of Infant and Toddler Development, Affordances in the Home Environment for Motor Development – Infant Scale, and the Canadian Occupational Performance Measure. Parent well-being will be monitored using the Depression Anxiety and Stress Scale.

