## Methods

A single blind RCT with 2 parallel groups will be conducted to evaluate the efficacy of GAME compared to standard care. The outcomes of this trial are the infant’s motor function after 16 weeks of intervention and at 12 and 24 months corrected age, home enrichment, parent perception of and satisfaction with their child’s performance and parental well - being.

We hypothesise that:Infants diagnosed with CP or at risk of CP that receive GAME intervention will have higher short term (after 16 weeks of intervention) Peabody Developmental Motor Scale (PDMS II) scores than infants that receive standard careInfants diagnosed with CP or at risk of CP that receive GAME intervention will have higher long term (at 1 year of age) scores on the PDMS II scores than infants that receive standard care.Infants diagnosed with CP or at risk of CP that receive GAME intervention will have higher Gross Motor Function Measure (GMFM) scores than infants that receive standard care at 1 year of age.Infants who have received GAME intervention will have sustained higher PDMS –II scores long term (at 24 months) compared with infants who have received standard care.

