### Study sample and recruitment

Thirty infants will be recruited from their treating institution, community physician or local therapist. The infants will be recruited in and around Sydney, NSW Australia. Seven NICUs and the Cerebral Palsy Alliance will actively recruiting to this study although infants may be referred from any source. Study sites are listed in the Appendix.

All parents of eligible infants will be informed about the study only after they have had discussions with their medical team regarding the high risk status of their child, or a confirmed diagnosis of CP. Families will be given a site specific information sheet regarding the purpose and design of the study and have opportunity to speak with investigators before consenting to the study. Parents who do not wish to consent to the study will be offered standard community based therapy.

After consent is obtained, prior to randomisation, the investigators will visit the family at home to complete all baseline assessments and collect demographic and perinatal data. MRI and medical data will be obtained from the infant’s medical record.

The Human Research and Ethics Committees of the Sydney Children’s Hospital Network (SCHN), Cerebral Palsy Alliance (CPA) and the University of Notre Dame Australia (UNDA) have approved this study. The experimental design including time points and outcome measures are depicted in the CONSORT [23] flowchart (Figure 1).

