### Randomization process

After informed consent and baseline measures are taken, an officer not connected with the study will randomise participants at a separate location using a pre-prepared random assignment schedule stored within 30 concealed opaque envelopes generated using computer generated random numbers. The Primary Investigator will be informed by the independent randomisation officer of group allocation and will inform parents. Twins will be randomised together due to the nature of the intervention.

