#### Canadian Occupational Performance Measure (COPM)

The COPM [44] is an individualised criterion referenced measure of performance of a self-selected range of activities. Functional problem areas are identified, prioritised and rated for performance and satisfaction via a semi-structured interview. The COPM will be used to prioritise goals and measure change in performance and satisfaction. The COPM will be used at baseline, 16 weeks after therapy has commenced and at 12 months. Data will be collected via face to face or phone interview by independent raters.

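### The 16-week primary assessment is timed from the start of therapy, which is undefined for standard care, so its timing may differ by arm

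*Protocol article*

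**What the plan says.** Wherever the text times the primary visit, the origin is the start of treatment:

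- Abstract, Methods/design: "Primary endpoint measures will be taken 16 weeks after intervention commences".
- Methods, first hypothesis: PDMS-2 scores in the "short term (after 16 weeks of intervention" sense.
- Outcome measures and procedures, PDMS-2: "PDMS-2 assessments will be obtained at baseline, 16 weeks after therapy has commenced and at 12 months and 2 years".
- Outcome measures and procedures, COPM: "The COPM will be used at baseline, 16 weeks after therapy has commenced and at 12 months".

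The DASS-21 is given at baseline and at every later time point, so it inherits the same 16-week visit.

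The article also describes two events that are common to both arms, baseline assessment and then allocation. Randomization process: "After informed consent and baseline measures are taken, an officer not connected with the study will randomise participants". Neither is used in the text to time the 16-week visit.

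On how treatment begins, the arms are described differently. Under Therapists, the investigators themselves deliver GAME, and under Environmental enrichment, "Home visits from the GAME treating therapists are offered weekly initially". Standard-care infants are treated by local therapists under each centre's own arrangements. The Standard care section says that frequency, intensity and type cannot be standardised, and its definition covers follow-up, therapy or both. Under Study sample and recruitment, "Thirty infants will be recruited from their treating institution, community physician or local therapist", so an infant may come to the trial through a therapist.

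**The concern.** A randomised comparison is protected when outcomes are measured at a time set by something both arms share. Here the clock starts at an event that the trial controls in one arm and leaves to outside services in the other. The article does not say what counts as the start of therapy for a standard-care infant who is already seeing a local therapist at entry, who waits for a first appointment, or who has follow-up only.

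At stake is the one primary comparison. If the rule is applied literally, time since randomisation and age at the visit can become a function of arm in infants whose motor skills are developing quickly. An infant with no therapy start would have no defined primary assessment date, which sits badly with the intention-to-treat analysis stated under Statistical methods.

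**Working it through.** The article gives no computed figure on this point to reproduce. The check sets the statements side by side and then does the simple timing arithmetic.

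**1. Is another origin stated?** No. The abstract, the hypothesis, the PDMS-2 section and the COPM section all use therapy or intervention. None uses baseline or randomisation.

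**2. Is the start of therapy comparable across arms?**

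| | GAME | Standard care |
|---|---|---|
| Who starts it | Trial therapists | Local services |
| Early schedule | Weekly visits offered at first | Not standardised |
| Possible start before randomisation | Not for GAME itself | Yes, if already in local therapy |
| Possible absence of therapy | Not foreseen | Definition allows follow-up only |
| Lag from randomisation given | No | No |

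**3. What follows for timing.** Let L be the lag in weeks from randomisation to the start of therapy, negative if therapy began earlier.

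- Visit time after randomisation = 16 + L weeks.
- Gap between arms = L(standard care) − L(GAME) weeks. Divide by 4.348 (30.4375 / 7) for months.

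With one common origin, L drops out. Every infant is seen at 16 weeks, which is 16 / 4.348 = 3.68 months after randomisation. Taking entry age (3 to 6 months corrected, Inclusion criteria) as age at randomisation, the visit falls at 3 + 3.68 = 6.68 to 6 + 3.68 = 9.68 months, and the gap between arms is zero apart from the visit window.

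To show how the rule behaves, and not as an estimate, take L(GAME) = 0:

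- L(standard care) = +4: the visit is at 20 weeks and the infant is 4 / 4.348 = 0.92 months older than a GAME infant who entered at the same age.
- L(standard care) = −4: the visit is at 12 weeks and the infant is 0.92 months younger.
- L(standard care) = −16: the visit coincides with randomisation.
- No therapy start: L is undefined, and so is the visit date.

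The sign of the gap is open. Its size needs start dates that the article does not give.

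**4. Would the analysis absorb a gap?** Statistical methods names MRI classification, socioeconomic status and comorbidities as covariates to be considered. Age at assessment and time since randomisation are not among them. The parents' log book is described as monitoring mode, frequency and intensity, and a start date is not named.

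**5. What is untouched?** The later PDMS-2, GMFM-66 and BSID-III assessments are set by age (12 and 24 months) in both arms. The sample size does not depend on the origin of the 16-week visit.

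**The case against.** The strongest reply is that the wording is loose and the design is sound. Baseline and randomisation come first, infants still in hospital are excluded, and standard care is what is offered after discharge. A sensible reader could take the phrase to mean 16 weeks of the allocated condition in each arm. The literal rule can even place the primary visit at randomisation, which suggests that nobody meant it literally. The flow chart showing the time points is not reproduced in the text at hand and may place the visit clearly. This has force and lowers confidence that the trial would go wrong in practice. It does not remove the point: the rule is stated, and repeated, in terms of therapy, and if practice counts from baseline, the text should say so.

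Three stronger readings are tempting and are not supported.

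- **That the arms would in fact be assessed at different times and ages.** No start lag is given for either arm, and both could be short.
- **That the pilot shows a delay in standard care.** The sentence "In the pilot study, SC therapy was offered approximately monthly but ranged from fortnightly to 3 monthly" describes how often sessions were offered. It says nothing about the wait for a first session.
- **That a bias in PDMS-2 points can be quoted and set against the pilot's 8.05-point difference.** This would need a rate at which scores drift with age, and the article gives none. The PDMS-2 is age-normed, so drift on a normed score could be near zero. Norming would not equalise time since randomisation, nor supply a date for an infant who never starts therapy.

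It is also fair to say that a follow-up-only control is a possibility under the definition of standard care and not an expectation: the Therapists section says that these infants will receive services from local therapists.

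**Conclusion.** The point holds as a defect in the stated timing rule. The 16-week primary PDMS-2, and the COPM and DASS-21 taken with it, are anchored to an event that the trial controls in one arm and that is undefined in the other. Applied as written, time since randomisation and age at the primary visit may differ by arm, in an unknown direction and by an amount the article does not allow to be estimated. The stated covariates would not correct it.

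This rests on reading the text literally and on standard-care start dates varying relative to randomisation, which the article makes possible but does not document. Confidence is moderate for that reason. The point is worth correcting because it touches the sole primary comparison and costs almost nothing. It does not show that the trial is biased, and it does not reach the 12- or 24-month results.

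**What to change.** State that the 16-week PDMS-2, COPM and DASS-21 are taken 16 weeks after randomisation (or after baseline, if that is preferred), identically in both arms and within one common visit window. Replace the references to therapy or intervention commencing in the abstract, the first hypothesis, and the PDMS-2 and COPM sections. Record the date of first therapy in both arms, for instance in the existing log book, and report it descriptively without using it to set visit dates.

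The cost is a short wording amendment and scheduling from the randomisation date. Treatment and sample size are unchanged. GAME infants may have had slightly less than 16 weeks of therapy at the visit, by whatever time passes between randomisation and the first home visit. If visits are already booked from baseline or randomisation, only the text needs to change.

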#### Gross Motor Function Measure (GMFM)

The GMFM [43] is a criterion-referenced tool that is widely accepted as the gold standard for gross motor assessment in children with CP. There are a total of 5 dimensions measured including rolling, sitting, creeping, standing and walking. Infants will be videoed during the assessment and blind raters will score from the video using the appropriate manual. The GMFM- 66 will be used in this study at the secondary endpoint, (12 months) and at the 2-year follow up.

#### Canadian Occupational Performance Measure (COPM)

The COPM [44] is an individualised criterion referenced measure of performance of a self-selected range of activities. Functional problem areas are identified, prioritised and rated for performance and satisfaction via a semi-structured interview. The COPM will be used to prioritise goals and measure change in performance and satisfaction. The COPM will be used at baseline, 16 weeks after therapy has commenced and at 12 months. Data will be collected via face to face or phone interview by independent raters.

#### Affordances in the Home Environment for Motor Development-Infant Scale (AHEMD-IS)

The AHEMD-IS [45] is a measure of the quality and quantity of motor enrichment opportunities available to a child within the home environment. This tool has demonstrated validity and reliability in the toddler format. Data is collected via a parent self report on a standardised questionnaire. A total raw score is calculated. This measure will be taken at baseline and at 12 months.

#### Depression, Anxiety and Stress Scale-21 (DASS)

The DASS-21 [46] is an adult self-report designed to measure the emotional states of depression, anxiety and stress. It is a 21-item questionnaire and will be used to measure parent emotional well-being at baseline, before randomisation and at all time points thereafter.

#### Bayley Scales of Infant and Toddler Development Third Edition (BSID-III)

The BSID-III [47] is a standardised and norm referenced assessment, which measures the cognitive, motor, language and social-emotional development of infants and toddlers aged 0–3. It consists of a number of developmental play tasks that can be completed at the child’s home and videoed for scoring by blind raters. Alternatively infants enrolled in follow up programmes from recruitment sites may be assessed by staff blinded to group allocation at their 1- year clinic appointment. Infants will be assessed on the BSID-III at 12 months and 2 years.

### Statistical methods

Analysis will be conducted on an intention-to-treat basis using SPSS and reported according to the CONSORT statement. Descriptive statistics (frequencies, means and 95% CIs) will be used to describe the sample at baseline and data from each outcome measure used will be summarised for both treatment groups. Between-group differences following intervention will be analysed using multiple regression to determine whether group allocation predicts outcome. MRI classification, SES and comorbidities including vision impairment and epilepsy will be considered as covariates in the analysis.

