### Sample size

The planned study sample size (n = 30; 15 per group) has been estimated from a power calculation based on our pilot data using motor composite scores of the PDMS-2, with an alpha value of 5% and power of 80%, using a minimal clinically important difference of 10%, accounting for a 20% dropout rate.

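### The regression named for PDMS-2 leaves out the baseline and earlier PDMS-2 scores and, without a further step, would omit infants lost by that visit

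*Protocol article*

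**What the plan says.** All references are to the protocol article.

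- **Statistical methods**: "Analysis will be conducted on an intention-to-treat basis using SPSS and reported according to the CONSORT statement". The comparison is then described in one sentence: "Between-group differences following intervention will be analysed using multiple regression to determine whether group allocation predicts outcome". On covariates: "MRI classification, SES and comorbidities including vision impairment and epilepsy will be considered as covariates in the analysis". Neither baseline PDMS-2 nor any earlier PDMS-2 score is on that list.
- **Peabody Developmental Motor Scales** subsection: "PDMS-2 assessments will be obtained at baseline, 16 weeks after therapy has commenced and at 12 months and 2 years".
- **Abstract, Methods/design**: "Primary endpoint measures will be taken 16 weeks after intervention commences".
- **Methods**: PDMS-2 hypotheses are stated at 16 weeks, at 1 year and at 24 months, the last as "Infants who have received GAME intervention will have sustained higher PDMS –II scores long term (at 24 months".
- **Sample size**: "The planned study sample size (n = 30; 15 per group", "accounting for a 20% dropout rate". The dropout figure is not tied to a visit.
- **Randomization process**: twins are allocated together.

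**The concern.** An ordinary regression takes one outcome per infant. Run as described, with nothing added, it has two weaknesses.

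First, it does not condition on baseline PDMS-2, usually the strongest predictor of a later score on the same scale. In a trial sized for about 24 evaluable infants, that gives up precision at every visit, including the primary one.

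Second, an infant with no score at 12 or 24 months drops out of that comparison, and the 16-week score already recorded for that infant is not used. Loss could plausibly differ by arm. Families know their allocation. GAME visits are offered weekly at first, whereas standard care in the pilot was roughly monthly. GAME stops at the first birthday, a year before the last assessment. If families in one arm leave according to how the infant is doing, the later comparisons are biased. The direction depends on the arm: losing poorly performing infants from standard care understates the benefit of GAME, and losing them from GAME overstates it.

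**Working it through.** **1. The plan's own dropout step.** With N = 30 and 20% dropout: 30 × 0.80 = 24 evaluable infants, 12 per group, and 24 / (1 − 0.20) = 30. The step reproduces. The full calculation cannot be checked, because no SD is given and the 10% difference is not anchored to a scale. For scale only: 12 per group at 80% power and two-sided 5% (t-test) corresponds to a standardised difference of 1.20. That value is derived here and is not stated in the article.

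**2. Assumptions for the bias.** The article gives none of these.
- PDMS-2 scores are standardised to SD 1, with correlation ρ = 0.7 between any two visits.
- Loss is 20%. In one arm it depends on the 16-week score, with log-odds slope 0.5, 1.0 or 1.5 per SD. In the other arm it is unrelated to score.
- The outcome is a later score (12 months; 24 months is the same if its correlations are the same).

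**3. Bias without baseline in the model.** Let m be the amount by which the completers' mean 16-week score exceeds the full arm's mean. The bias in the later difference is ρ × m. Simulation gives a bias of 0.067, 0.122 and 0.158 SD for the three slopes, so m = 0.067/0.7 = 0.096, 0.122/0.7 = 0.174 and 0.158/0.7 = 0.226.

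**4. Bias with baseline in the model.** Given baseline, the coefficient of the later score on the 16-week score is ρ/(1 + ρ) = 0.7/1.7 = 0.41. The completers' shift left after baseline is (1 − ρ²) × m = 0.51m. The bias is therefore about 0.41 × 0.51 × m = 0.21m:

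| Slope | m | No baseline | With baseline | Likelihood model using 16-week score |
|---|---|---|---|---|
| 0.5 | 0.096 | 0.07 | 0.02 | about 0 |
| 1.0 | 0.174 | 0.12 | 0.04 | about 0 |
| 1.5 | 0.226 | 0.16 | 0.05 | about 0 |

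Direct simulation of the three models agrees with the table. Against 1.20 SD, the bias is 0.07/1.20 = 6% to 0.16/1.20 = 13% without baseline, and 0.02/1.20 = 2% to 0.05/1.20 = 4% with it.

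**5. Sensitivity.** A separate simulation of 30 infants, with its own dropout rule and correlations from 0.5 to 0.85, gave a bias of 0.05 to 0.09 SD for one-arm loss even with baseline in the model. The likelihood analysis removed it. When loss depended on score equally in both arms, the bias was negligible (at most 0.007 SD).

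**6. Precision.** With 12 per group, SE = √(2/12) = 0.41 SD without baseline. With baseline it is 0.41 × √(1 − 0.7²) = 0.41 × 0.714 = 0.29 SD. Adding the 16-week score to a baseline-adjusted analysis changes little: in the 30-infant simulation the SE fell from 0.304 to 0.300 at correlation 0.7.

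**The case against.** A reader might infer that the article plans a completers' analysis, visit by visit, and mislabels it as intention-to-treat. The text does not support that. It does not say that a separate model is fitted at each visit or that infants with missing scores are excluded. Regression by allocated group is compatible with intention-to-treat and could follow imputation. Missing-data rules are also commonly left to a full protocol or analysis plan, and neither is shown, so their absence here is not the point. What remains is narrower: the article does name a model and a covariate list, and neither includes the earlier PDMS-2 scores.

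A reader might also take the word sustained in the 24-month hypothesis as a longitudinal claim that regression cannot test. The hypothesis compares the two groups at 24 months, and a regression of the 24-month score on group addresses that.

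Three further objections stand in part:
- The bias needs score-dependent loss in one arm only, and nothing in the article gives dropout by arm. Even then it is well below one standard error (0.29 to 0.41 SD).
- The sample is already inflated for dropout, and the 20% need not fall before 16 weeks, so the threat is mainly to the 12- and 24-month comparisons.
- A mixed model with baseline as a covariate gains nothing from an infant with no post-baseline score. It does not rescue early dropouts at the primary endpoint, which is why a sensitivity analysis is needed as well.

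**Conclusion.** The point holds as an avoidable weakness of the stated model. It is not a contradiction with the intention-to-treat claim.

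- **Bias.** Under 20% loss, correlation 0.7 and score-dependent loss in one arm only, the 12- and 24-month differences would be biased by about 0.07 to 0.16 SD with the covariates as listed. Here the listed covariates are taken to carry none of the earlier-score information. Adding baseline PDMS-2 cuts this to 0.02 to 0.05 SD, and a likelihood model that also uses the 16-week score brings it to about zero. If loss depends on score equally in both arms, there is essentially nothing to correct.
- **Primary endpoint.** The 16-week result is little affected by the choice of a repeated-measures model. What helps it is baseline adjustment, which on the same correlation reduces the standard error by nearly 30% (0.41 to 0.29 SD).

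The change is worth making because the data are already collected and the cost is low. The effect on the later comparisons is modest and conditional.

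**What to change.** Analyse PDMS-2 in all infants as randomised with one linear mixed model for repeated measures over the 16-week, 12-month and 24-month scores. Include visit, group, group-by-visit and baseline PDMS-2, with a family effect if twins enrol. Take the 16-week group contrast as primary and the 12- and 24-month contrasts for the second and fourth hypotheses. Add one delta-shift sensitivity analysis: impute missing scores, including those of infants with no post-baseline score, and shift them by a stated range in one arm to see when the conclusion changes.

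If an unseen analysis plan already specifies imputation or a longitudinal model with baseline PDMS-2, one sentence in the Statistical methods section saying so is enough.

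The cost is a change of wording and modest programming; SPSS MIXED fits the model. No extra data are needed. The model assumes that scores are missing at random given the observed scores, and the delta-shift analysis probes that assumption. The main gain in precision will come from baseline adjustment rather than from the repeated measures.
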